### Randomisation

All children who meet the inclusion criteria after the screening visit will be randomised to either the control or intervention group. Generalised block randomisation including 10 participants per block will be performed by a computer program, with an allocation ratio of 1:1 [23]. Because this is a lifestyle study, blinding is not possible.

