### Statistics

#### Sample size calculation

Earlier studies on weight loss in asthmatic adults demonstrated improvements in FEV_1_ of 8% and 6% respectively [65,66]. In adolescents with asthma, improvements in FEV_1_ of up to 24% were found after a weight reduction program [67]. In total, 104 participants are sufficient to detect a change of 5% in FEV_1_%, assuming a five-repeated measurement design of Hedeker et al., a two-sided alpha of 5%, a correlation between measurements of 0.7, a power of 80%, a sample size ratio of 1:1, a drop-out rate of 5% and an autoregressive(1) variance-covariance matrix structure [68].

According to the Fleisch method of power calculation, 80 participants are sufficient to detect a clinical relevant decrease of 0.25 BMI-SDS, with a two-sided alpha of 0.05, a drop-out rate of 20% and a power of 90% [69].

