## Discussion

This paper describes the design of the Mikado study, an RCT testing the effects of a multifactorial weight loss intervention on asthma parameters in children with overweight and asthma. The multifactorial intervention consists of sessions concerning diet and behaviour, sport, parental involvement and individual counselling. Emphasis is put on individual goal setting, positive reflections and reinforcements. The efficacy of the Mikado study will be measured by regular anthropometric and lung function measurements. In addition, this study should provide enhanced understanding of the underlying pathophysiology of the asthma-obesity relation in children.

The Mikado study is, up to now, the first RCT to investigate the effects of a weight reduction intervention on asthma parameters in children. Strengths of the Mikado study include its long duration, its broad range of outcome measures and the fact that the intervention is comprised of successful components of previous studies.

There are several critical success factors that should be mentioned. Previous lifestyle studies in children have frequently reported recruitment problems and dropout rates as high as 42% [51,70]. The main reasons for these were parental attitudinal issues, such as denial that their child would benefit from improved nutrition and exercise, inflexibility in making room in the family’s schedule for the program, prohibitive costs and an unwillingness to change the home environment. We will try to minimise these barriers for recruitment by training the researchers in telephonic skills, and by inviting hesitant participants for a personal informative meeting regarding the study. Offering an individualised programme and closely monitoring the participants by the intervention team should minimalize dropout. In case of high dropout rates, we will perform a responsive evaluation to investigate the reasons [71].

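### A single fixed block size of 10 in an open trial makes about 17 of 104 allocations deducible to anyone who knows the block size and sees the ordered allocations

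*Protocol article*

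**What the plan says.** The Randomisation section of the protocol article fixes the method in a few sentences. On who is randomised and when: "All children who meet the inclusion criteria after the screening visit will be randomised to either the control or intervention group". On the method: "Generalised block randomisation including 10 participants per block will be performed by a computer program, with an allocation ratio of 1:1". On masking: "Because this is a lifestyle study, blinding is not possible". It gives one block size, mentions no variation in size and describes no stratification. The sample size section plans for 104 children.

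Two other places bear on the point. The Discussion says that recruitment barriers will be reduced by training researchers in telephone contact and by "inviting hesitant participants for a personal informative meeting regarding the study". It also cites drop-out of up to 42% in earlier lifestyle studies of children, attributed mainly to parental attitudes. In Table 1 the only rating of motivation is made by the sport instructor after sport sessions. It therefore exists only in the intervention arm and only after randomisation.

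**The concern.** With a constant block size and an open trial, the end of each block follows from its beginning. Once five children in a block have gone to one arm, every remaining place belongs to the other. A person who knows this and can influence when or whether a family completes screening could match families to places.

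The natural trait to select on here is motivation. The article itself treats parental attitude as a main cause of failed recruitment and drop-out, and the intervention asks a great deal of families for 18 months. If more motivated families entered the intervention arm, both FEV1 % predicted and BMI-SDS could be affected through adherence and prognosis. No baseline measure of motivation is listed, so such an imbalance could be neither seen in the baseline table nor adjusted for.

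**Working it through.** The block size is a design choice, so the plan has no derived figure to reproduce. The check is how predictable the stated scheme is.

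**Inputs**
- Block size 10, ratio 1:1, hence 5 + 5 per block (Randomisation).
- No blinding (Randomisation).
- N = 104, which is ten full blocks plus four children (Sample size calculation).
- Assumption: standard permuted blocks. The source cited for the generalised block method is not at hand.
- Assumption: the observer knows the block size and sees all earlier allocations in order.

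**Allocations known with certainty, fixed block of 10**

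There are C(10,5) = 252 equally likely blocks. A position is determined when it and all later positions in the block go to the same arm:
- 10th: always (100%)
- 9th: 2·C(8,3)/252 = 112/252 = 44.4%
- 8th: 2·C(7,2)/252 = 42/252 = 16.7%
- 7th: 2·C(6,1)/252 = 12/252 = 4.8%
- 6th: 2/252 = 0.8%
- 1st to 5th: never

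The sum is 1 + 0.444 + 0.167 + 0.048 + 0.008 = 1.667 per block. This agrees with the closed form 2m/(m+1) = 10/6 for m = 5. Over ten full blocks it gives 16.7 allocations. The last four children fall in the first half of an eleventh block and add none, so 16.7/104 = 16.0% of the trial.

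**Best-guess accuracy, fixed block of 10**

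Always guessing the under-represented arm gives m + (2^(2m)/C(2m,m) − 1)/2 = 5 + (1024/252 − 1)/2 = 6.53 correct per 10, or 65.3% against 50% by chance. For 104 children, the first four places of the eleventh block add 0.500 + 0.556 + 0.556 + 0.595 = 2.21 expected correct guesses. Then (65.32 + 2.21)/104 = 64.9%.

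**Other fixed sizes**

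| Fixed size | Certain | Best guess correct |
|---|---|---|
| 4 | 33.3% | 70.8% |
| 6 | 25.0% | 68.3% |
| 8 | 20.0% | 66.6% |
| 10 | 16.7% | 65.3% |
| 12 | 14.3% | 64.3% |

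**Randomly varying sizes** (1,000 simulated trials of 104; the observer knows the set of possible sizes but not the current one)

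| Sizes | Certain, of 104 | Share | Best guess correct |
|---|---|---|---|
| 10 (fixed) | 16.7 | 16.0% | 64.9% |
| 4, 6, 8 | 2.5 | 2.4% | 67.8% |
| 6, 8, 10 | 1.8 | 1.7% | 66.1% |
| 8, 10, 12 | 1.4 | 1.4% | 65.0% |

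Varying the size removes most certain deductions. It does not reduce informed guessing, and small sizes make guessing easier.

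**The case against.** The strongest reply is that the harm depends on facts the article does not give. An open trial does not mean that recruiters see a trial-wide, ordered list. Children come from four sources, including paediatricians at three hospitals, so a useful tally needs central knowledge of the order and of the block boundaries. Allocation is by computer program, after eligibility has been checked at screening, and covers every eligible child. Nothing says who runs the program, who schedules screening visits, or that these are the people who talk to hesitant families. Who holds the list and how allocations are released are details that an article commonly leaves to the full protocol. Ten is also a fairly large block, and fixed blocks of 4 or 6 would be worse.

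All of this stands, and it makes the risk conditional. It does not remove the point, which rests on what the article fixes (one constant size, 1:1, in an open trial) and not on what it omits.

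A reader might go further and infer that staff can work out upcoming allocations in general, that publication gave the block size away during enrolment, or that allocation was not concealed. The documents support none of these. Certainty is confined to about one allocation in six, late in each block. The article does not say whether enrolment was still open when it appeared. Its silence on concealment is not evidence of a defect.

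**Conclusion.** The point holds as a conditional weakness of a stated design choice. Under standard permuted blocks, and for someone who knows the block size and sees the sequence, 1.67 of every 10 allocations (16.7 of 104) are certain in advance. The best guess is right about 65% of the time. The tenth place in every block is always known.

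These figures measure predictability, not bias. The documents do not allow any estimate of a resulting shift in FEV1 % predicted or BMI-SDS, and they do not show that anyone used or could use the sequence. The change is still worth making, because a better scheme costs almost nothing and selection on motivation could not be detected or corrected from the baseline measures listed.

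**What to change.** For all children still to be randomised, replace the constant block of 10 with block sizes drawn at random from a larger set, for example 8, 10 and 12, and do not disclose the sizes to recruiting staff. This cuts certain allocations from 16.7 to about 1.4 of 104 with best-guess accuracy unchanged at 65%. Do not use 4, 6 and 8: certain allocations fall to about 2.5, but accuracy rises to about 68%.

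Varying the size leaves informed guessing in place, so the running tally should also be kept from recruiting staff. If the full protocol already provides for this, a sentence saying so would remove most of the concern, including for children already randomised.

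The cost is one setting in the randomisation program and a slightly larger possible imbalance at the end of enrolment. With fixed blocks of 10 the arms can differ by at most 4 at N = 104 (four children in the open block), or by 5 at any other stopping point. With blocks of up to 12 they can differ by at most 6.

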### Outcome measures

An overview of all the outcome measurements and corresponding time points can be found in Table 1.

#### Lung function measurements

Maximal Expiratory Flow Volume (MEFV) curves will be measured with a spirometer (ZAN Messgerate, Oberthulba, Germany) according to American Thoracic Society / European Respiratory Society (ATS/ERS) guidelines [24]. LABA will be withheld 48 hours and SABA 8 hours before the measurement. During these measurements all children will be instructed by experienced researchers and nurses specialised in lung function measurements. The highest value of 3 technically appropriate measurements will be recorded and predictive values will be calculated according to prediction formulas of Zapletal et al. [25]. Reversibility will be defined as a change of ≥9% in FEV_1_ after 400 μg of extra-fine salbutamol (Airomir, Teva Pharma, Leiden, the Netherlands). During T0 reversibility will be determined after the completion of the BHR test.

Static lung function indices will be determined by body plethysmography (Viasys, Hoechberg, Germany) according to the ATS/ERS guidelines [24]. BHR will be determined by a histamine provocation test. A dose of histamine will be increasingly administered until a drop of 20% of the FEV_1_ is obtained or until a dose of 16 mg/ml histamine is reached [26]. The provocative concentration that will lead to a drop of 20% of the FEV_1_ (PC20) will be determined by linear interpolation of the last 2 points on the log dose–response curve.

#### Anthropometric measurements

Children will be weighed while wearing underwear and without shoes. Length will be measured twice to the nearest 0.5 centimetre (Stadiometer model 213, Seca, Birmingham, United Kingdom). Weight will be measured twice to the nearest 0.1 kilograms using a medical calibrated weight scale (Model 877, Seca, Hamburg, Germany). The average weight and height measurement will be used to calculate the BMI. BMI-SDS scores will be defined by the LMS-method of Cole et. al [20] based on the reference charts of the Dutch fourth Nationwide Growth Study [21].

Skinfold thickness will be derived from the triceps, biceps, subscapular and supra iliacic skinfolds by a Skinfold Calliper (Harpenden, British Indicators, Sussex, United Kingdom). Fat percentages will be generated by using the formulas of Deurenberg et al. [27]. Waist-hip ratio will be obtained by measuring the hip and waist circumference for each visit. Both skin fold thickness and waist-hip circumference measurements will be performed twice according to international guidelines [28].

#### Maximal ergometry test

All patients will perform a maximal incremental ergometer test (Reha Ergometer, Ergoline, Bitz, Germany) by using a continuous ramp protocol [29]. LABA will be withheld 48 hours and SABA 8 hours before the maximal ergometry test. During the test, breath by breath gas exchange will be analysed by a mass spectrometer (Oxicon Pro, Carefusion, Hochberg, Germany), and Heart Rate (HR) by means of a continuous 12-lead electrocardiogram (Masterscreen ECG, Carefusion, Hochberg, Germany).

The pedalling frequency will be held at 60 rpm and participants will be encouraged during the test to continue as long as possible. At the start, children will rest for 3 minutes in seated position followed by 3 minutes of cycling at the first increment, which is determined by length. Children below 120 cm will undergo a protocol with 10 W/min increment, children 120–150 cm will undergo a protocol with 15 W/min and a 20 W/min increment will be used in children >150 cm.

During the test, the wattage will incrementally increase until children can no longer continue the pedalling frequency for at least 5 seconds, or if termination is required according to other standard safety criteria. After exhaustion, children will continue to cycle for 3 more minutes at the first increment. The test will be accepted if at least 2 of the following criteria will be reached: 1. <2 ml/kg/min increase in oxygen uptake (VO_2_) with increasing work load, 2. Respiratory Exchange Ratio > 1.00, 3. HR ≥85%predicted (as assessed by 220 minus age). During the test the following variables will be measured: HR, Minute ventilation (V’E) and VO_2_ in L/min and in L/min/kg bodyweight. The Anaerobic Threshold will be determined by the V-slope method as described by Beaver et al. [30], predicted values will be calculated according to normal values of Ten Harkel et al. [31].

MEFV curves will be determined by a spirometer (ZAN Messgerate, Oberthulba, Germany) before exercise, 10 and 30 minutes after completion of the maximal exercise test. The severity of EIB will be measured as the difference in pre-exercise and post-exercise FEV_1_.

#### Questionnaires

Information on socio-demographic characteristics such as age, sex, ethnicity, parental BMI, social economic status and smoking exposure will be collected. Asthma control will be measured by the Asthma Control Test (ACT) in children >11 years [32]. The childhood ACT (C-ACT) will be used in children ≤11 years [32,33]. A score of ≤19 will be defined as uncontrolled asthma [34]. Medication use will be evaluated over the 2 months period prior to the clinic visit and dose equivalents will be calculated according to standard dosage of SABA, LABA and ICS [16,17,35,36]. The GINA guidelines will be used to determine asthma severity (intermittent, mild, moderate and severe) based on the intensity of treatment [37]. A Dutch questionnaire and the ISAAC questionnaire will be used to measure asthma symptoms [38]. Asthma-related quality of life will be measured by the Paediatric Asthma Quality of Life Questionnaire (PAQLQ) [39]. According to the PAQLQ guidelines, the minimal important difference will be defined as a difference of 0.42 points [40]. The Euroqol 5D Youth version will be used as a measurement tool for general health related quality of life [41].

To investigate commonly associated morbidity in children with asthma, sleep related breathing disorders will be assessed by means of the Paediatric Sleep Questionnaire (PSQ) [42]. A score of >0.33 will be defined as having a high risk for developing a sleep-related breathing disorder [42]. The existence of Gastro-Oesophageal Reflux Disease (GERD) symptoms will be assessed by the GERD questionnaire [43]. A suspicion of GERD is present when the score is ≥ 3 points [43]. Psychosocial problems will be determined by an abnormal score on the Dutch version of the Strength and Difficulties Questionnaire (SDQ) according to the SDQ scoring guidelines [44]. In addition, the Dutch Eating Behaviour Questionnaire (DEBQ) will be used to determine whether children have high scores on the subscales: Emotional Eating (13 items), External Eating (10 items) or Restrained Eating (10 items) [45].

#### Atopy, systemic and airway inflammation

Systemic inflammation will be determined in blood serum. The serum concentration of leptin will be determined in 100 microliter of plasma by means of multiplex immunoassay (Luminex Corporation, Austin, TX, USA). Airway inflammation will be measured by means of Fractional exhaled Nitric Oxide (FeNO) and markers in Exhaled Breath Condensate (EBC). FeNO will be obtained with the online NIOX analyser (Aerocrine, Solna, Sweden) according to international guidelines [46]. EBC will be collected by means of an optimised glass tube, cooled by counter-current circulating ice water as described previously [18]. In short, children will breathe tidally into the cooled glass tube for 10 minutes, while wearing a nose-clip, through a mouthpiece connected to a 2-way non-rebreathing valve. Subsequently, acidity will be measured and the EBC samples will be frozen by using dry ice and stored at −80°C. Levels of various cytokine, chemokines, and soluble intercellular adhesion molecule-1 (sICAM-1) will be measured in 100 microliter EBC with multiplex immunoassay (Luminex, Luminex Corporation, Austin, USA) [47].

#### Physical activity and dietary behaviour

Physical activity level will be measured as the average step count per day measured over a week. All children will be instructed to wear a triaxial accelerometer (Yamax EX510 Power Walker, Yamax, Tokyo, Japan) for 7 consecutive days. While wearing the accelerometer, all children will keep a diary about the time spent on swimming and cycling.

Dietary intake will be measured by means of 3-day food records. Parents and children will receive a standardised instruction based on the multiple-pass method about fulfilling dietary records at the start of the study [48]. An online program (Vodiweb, Vodisys Medical Software, Groningen, The Netherlands) will be used to calculate nutrition composition, based on Western and local food tables and normalised portion sizes [49]. The purpose of this tool is to measure intake of energy and macronutrients (fat, carbohydrate, protein) as well as to differentiate between healthy and unhealthy snacking during the day. A trained researcher will check all food diaries for completeness.

### Intervention

We incorporated the most effective components of current weight reduction programs for children in our intervention [50-53]. Several reviews and meta-analyses concluded that long-term (>1 year) multi-component lifestyle interventions targeted at both children and caregivers are most efficient [50-53]. The health counselling model is the theoretical basis of our intervention [54]. The most important components of this intervention are sport sessions, lifestyle sessions including dietary advices and cognitive behavioural therapy, parental sessions, and individualised counselling. Children will be divided in small groups of 8 to 12 children. Intervention group allocation will occur according to place of residence and age (6–11 years and 12–15 years). To secure that intervention professionals adhere to the protocol, all intervention professionals will meet on a regular basis with a study coordinator as supervisor. The intervention is divided in an initial phase (months 0–6) and a follow-up phase (months 7–18) (Figure 1).

#### Theoretical basis of intervention

The theoretical foundation of the intervention is derived from the health counselling model [54]. Health counselling is a model in which 3 phases for lifestyle changes are included: preparations, behaviour change and follow-up. The initial (preparation and behaviour change) phase will be imbedded during the first 6 months of the intervention in which there are frequent contact moments; the follow-up phase will be imbedded in the last 12 months (Figure 1). In each phase, well-known behavioural change theories such as the Stages of Change Model, Theory of Planned Behaviour, Social Cognitive Theory and Relapse Prevention Model are imbedded [55-58]. The preparation phase consists of 3 steps: 1. awareness (e.g. unhealthy eating and sedentary behaviour leads to obesity, which leads to health problems and stigmatising), 2. consideration of the new behaviour (e.g. benefits and disadvantages of losing weight) and 3. decision making (e.g. shared decision making including detecting and removing barriers). During the behaviour change phase children will receive more information about healthy behaviour and will be encouraged in each session to set a specific goal which they add to their personal goal list (e.g.: ‘I will walk the dog at least 4 days a week for 30 minutes’). In the follow-up phase children will learn how to preserve their behaviour (e.g. creating reminders of their goal-lists in their home environment, avoiding risk situations, learning social and coping skills) and eventually relapse strategies will be made (e.g. making a ‘first aid box for difficult situations’).

#### Sport sessions

Sport sessions will consist of regular group exercises (twice a week during initial phase, three times a month during the follow-up phase, Figure 1), with a duration of 60 minutes per session. All sport sessions will be guided by an experienced paediatric physiotherapist or a paediatric sport instructor. A session will consist of 10 minutes warming-up, 20 minutes aerobic exercises, 20–25 minutes interval exercise games and 5 minutes cooling-down. In order to offer an enjoyable program, several recreational sports will be played such as basketball, soccer, rope skipping, and tag games. The duration and intensity of the exercises will gradually increase during the first 3 months of the exercise program. Intensity of the exercise will be held at 60-75% of the age-adjusted maximal HR. All participants will wear a heart rate monitor (polar FS3c, Polar Electro Oy, Kempele, Finland,) during each sport sessions. During and after the sport sessions the (average) HR of each participant will be evaluated by the sports instructor. In addition, Borg’s perceived exertion scale is used to monitor exertion [59]. If advised by the children’s physician, sport instructors will encourage participants to use SABA 15 minutes before exercise.

During the initial phase participants will be motivated by their sports instructor to choose a supervised sport in their own environment, which children will practice during the follow-up phase. All participants will be encouraged to visit at least 3 different sport clubs in the vicinity of their residence. Folders with sport facilities in the environment will be provided. All parents will be encouraged to support their child to find a new sport during the parental sessions.

